#### Secondary outcomes

##### Safety

Hypothermia (<36 °C), respiratory failure requiring acute intubation, and/or cardiopulmonary resuscitation (CPR).

##### Physiological stability

Physiological variables are recorded during the first 24 hours (Table 1).

##### State-Trait Anxiety Inventory (STAI)

Maternal anxiety is measured with STAI Form Y [34]. STAI measures state and trait anxiety [35]; the mothers answer this questionnaire before the infants are discharged from the hospital, and when the child is 3 months and 2 years (corrected age). The questionnaire consists of 20 statements that evaluate how the mother feels ‘at this moment’ and twenty statements that evaluate how the mother feels ‘generally’. All items are scored according to a 4-point Likert scale

##### General Movement Assessment (GMA)

All infants are videotaped at 10–15 weeks post term age (fidgety movements’ period) for the GMA and the AMR. The video recordings are performed and classified according to the Prechtl method [36, 37] by a certified GMA observer unaware of the intervention group.

##### Ages & Stages Questionnaire - Social-Emotional (ASQ-SE)

The child’s social and emotional competence is evaluated using the ASQ-SE at corrected age of 3 months and 2 years [38]. The ASQ-SE comprises 22 questions that address seven behavioral areas: self regulation, compliance, communication, adaptive functioning, autonomy, affect, and interaction with people. The ASQ-SE is a screening instrument developed for children aged 3 months to 5 years.

#### Clinical registration

A case report form (CRF) has been prepared in cooperation with the Unit for Applied Clinical Research at the Norwegian University of Science and Technology (NTNU). The CRF is divided into three parts.On admission and the first 24 hours:Background data which are recorded are: mode of delivery, GA, sex, Apgar scores at 1, 5 and 10 minutes, birthweight, length, head circumference, maternal cause of preterm delivery (preeclampsia, breech position, rupture of membranes, premature contractions or infection), fetal cause of preterm delivery (growth retardation, non-reassuring CTG registration), and antenatal steroids (full or incomplete course).Observations and interventions which are recorded during the first 24 hours are: oxygen saturation and requirement, mode of breathing support (hourly), surfactant administration, time of SSC after birth and any cause for interrupted SSC before 120 minutes, age at the first feed (gavage or oral), any intravenous infusion, transcutaneous carbon dioxide and total amount of enteral and parenteral nutrition given. Blood pressure is measured once during the first 120 minutes.Adverse events: the safety is closely monitored by the consultant and the neonatal nurse present. It will be registered as an adverse event if body temperature drops <36.0 C° or if the infants have signs of any respiratory failure requiring interventions in addition to an interruption of SSC and transfer to the NICU for a higher level of monitoring and/or respiratory support.During hospitalization:Variables recorded are: daily weight, age on removal of feeding tube, time in skin-to-skin position every day, all nutrition (parenteral and enteral), any insulin given, any surgery, mechanical ventilation (mode and duration), CPAP/bilevel positive airway pressure (BiPAP) (duration), supplemental oxygen and/or ventilator support at 28 postnatal days, 36 and 40 weeks postmenstrual age (BPD), any sepsis (with maximal CRP and duration of antibiotic), cerebral ultrasound and magnetic resonance imaging (MRI) results (IVH or PVL), seizures, NEC, treatment for PDA and postmenstrual age (PMA) for transfer from intermediate to the step-down unit in the NICU.At discharge:Variables recorded are: PMA, weight, length, head circumference and mode and type of nutrition. At St. Olav’s Hospital, families living less than 30 minutes by car from the hospital are offered home care with gavage feeding for infants from PMA 34 weeks. Criteria for participation for the infants are: full enteral feeds; no apneas/bradycardias requiring caffeine or monitoring; stable body temperature and positive weight gain. A family is invited to participate in the home care program if there are two caregivers at home during the day and at least one of them speaks Norwegian or English.

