**Methods/Design:**

A randomized controlled trial (RCT) of skin-to-skin care in the delivery room for very preterm infants born at gestational age 28^0^–31^6^ weeks with birth weight >1000 grams. Infants with severe congenital malformations or need of intubation in the delivery room are excluded. A detailed checklist and a flowchart were prepared for the study, and all involved professionals (neonatologists, neonatal nurses, obstetricians, anesthesiologists, midwives) participated in medical simulation training prior to study start on February 1, 2014. A consultant in neonatology and a neonatal nurse are present at all deliveries. Infants with birth weight <1500 grams receive an intravenous line with glucose, amino acids, and caffeine citrate in the delivery room. Infants with gestational age <30 weeks are routinely put on continuous positive airway pressure (CPAP). After initial stabilization, infants are randomized to skin-to-skin care or are transferred to the nursery in an incubator. Primary outcome is cognitive development at 2 years measured with the Bayley Scales of Infant Development, Third Edition. Secondary outcomes are safety defined as hypothermia, respiratory failure, and/or cardiopulmonary resuscitation, physiological stability after birth and motor, language and cognitive development at 1 year for the child, and mental health measured with the State-Trait Anxiety Inventory (STAI) at discharge, and at 3 months and 2 years after expected date of delivery for the mothers.

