#### Secondary aims

To assess safety of the intervention by measuring incidence of hypothermia (temperature <36 °C) or respiratory failure during the first 2 hours of life.To estimate the effect of the intervention on complications to prematurity (intraventricular hemorrhage (IVH) or periventricular leukomalacia (PVL), seizures, necrotizing enterocolitis (NEC), treatment for persistent ductus arteriosus (PDA), and bronchopulmonary dysplasia (BPD)).To estimate the effect of the intervention on physiological stability during the first 24 hours.To estimate the effect of the intervention on maternal mental health at discharge from the NICU and when the child’s corrected age is 3 months and again at the corrected age of 2 years by using the State-Trait Anxiety Inventory (STAI).To investigate if the intervention affects the fidgety type of general movements and detailed aspects of the early motor repertoire at the corrected age of 3 months, using the General Movement Assessment (GMA) and the Assessment of Motor Repertoire – 2 to 5 months (AMR).To estimate the effect of the intervention on neurodevelopmental outcomes including cognition, language, and motor function at the corrected age of 1 year, and language and motor function at the corrected age of 2 years assessed with Bayley-III.To investigate the effect of the intervention on social and emotional competence at the corrected age of 3 months and at 2 years with the Ages & Stages Questionnaire - Social-Emotional

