### Intervention

For all infants of eligible women, cord milking is advised immediately following delivery and before the infant is placed on the resuscitation unit. Predefined blood samples are taken from the umbilical cord. Blood gas is taken from the umbilical artery before cord clamping, while blood for hemoglobin, leukocytes, thrombocytes, C-reactive protein (CRP) and blood typing is sampled after the cord clamping.

After the initial stabilization, the infant is treated and evaluated according to checkpoint 1 on the checklist, and eligibility is decided by the consultant (Fig. 1). Infants randomized to standard care are transferred to the NICU in an incubator after stabilization. The father will usually follow the newborn to the NICU, while the mother will come as soon as possible after delivery.

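### The respiratory adverse event is worded around interrupted skin-to-skin care and transfer to the NICU, has no standard-care equivalent, and does not match the stated safety aim or outcome

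*Protocol article*

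**What the plan says.** Safety is described in four places in the Protocol article.

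- **Abstract, Methods/Design:** "safety defined as hypothermia, respiratory failure, and/or cardiopulmonary resuscitation", with no severity criterion and no time window.
- **Secondary aims (first aim):** "incidence of hypothermia (temperature <36 °C) or respiratory failure during the first 2 hours of life". CPR is not mentioned.
- **Secondary outcomes, Safety:** hypothermia below 36 °C, plus "respiratory failure requiring acute intubation, and/or cardiopulmonary resuscitation (CPR"). No time window is given.
- **Clinical registration, Adverse events:** "It will be registered as an adverse event if body temperature drops <36.0 C"°, or if there are signs of "any respiratory failure requiring interventions in addition to an interruption of SSC and transfer to the NICU", the transfer being for closer monitoring or more respiratory support. CPR is not named. The item sits in the part of the case report form for admission and the first 24 hours but has no window of its own.

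The care pathways differ by design. Under Intervention, "Infants randomized to standard care are transferred to the NICU in an incubator after stabilization", whereas SSC infants are offered up to 2 hours of SSC in the delivery or recovery room. The consultant and neonatal nurse present monitor safety. The Discussion states that NICU staff caring for the infant in the first 24 hours are not masked.

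**The concern.** Whether SSC after delivery is safe is part of the study's stated aim, and safety is the first secondary aim. A between-arm safety comparison needs an event that infants in either arm can have and that is recorded by the same rule in both. The respiratory part of the adverse-event rule is instead expressed through two things that happen only on the SSC pathway: stopping SSC, and a later move to the NICU because more support is needed. If registered events were compared between arms, SSC could look harmful because of the wording alone.

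The second problem is that event counts depend on the section followed. An infant whose respiratory failure is managed without intubation may count under the aim and under the adverse-event rule, but not under the outcome. A temperature below 36 °C at 10 hours counts under the outcome but not under the aim.

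**Working it through.** **1. The definitions side by side**

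| Section | Respiratory criterion | CPR | Time window | Temperature |
|---|---|---|---|---|
| Abstract | respiratory failure, unspecified | yes | none | hypothermia, no threshold |
| Secondary aims | respiratory failure, unspecified | no | first 2 hours | <36 °C |
| Secondary outcomes, Safety | requiring acute intubation | yes | none | <36 °C |
| Clinical registration | requiring interventions, tied to SSC interruption and NICU transfer | not named | none of its own | <36.0 °C |

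The three sections in the body of the article agree only on the 36 °C threshold. The direct conflict is between Secondary outcomes and Clinical registration. Secondary aims differs mainly in scope: it sets a window and leaves severity open. The window also matters for temperature, because Table 1 schedules readings at 15, 30, 60 and 120 minutes and again at 10 and 18 hours.

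**2. Can a standard-care infant meet the adverse-event criterion?**

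- *Literal reading* (failure needing intervention, together with SSC interruption and NICU transfer): no. The infant has no delivery-room SSC and has already gone to the NICU by protocol. Skin-to-skin contact later in the NICU does not change this, because no transfer to the NICU can follow.
- *Lenient reading* (interventions beyond merely stopping SSC and moving the infant): possibly. The rule does not say what would count for an infant who was never in delivery-room SSC, and the interventions are undefined.

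The two readings can also give different counts within the SSC arm.

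**3. Possible size on the literal reading (illustration only)**

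Inputs from Sample size and statistical analyses: 68 per group; Pearson chi-square or Fisher's exact test for categorical variables; P < 0.05. The plan's own figure reproduces: a difference of 7.5 with SD 15, two-sided α = 0.05 and 80% power needs 63.8 per group by the t test, so 64, raised to 68. That calculation concerns the Bayley-III cognitive score; no safety event rate or safety power is stated.

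Assumptions: the same true rate p in both arms (5%, 10%, 20%); all SSC events and no standard-care events registered; infants independent, which ignores that twins share an allocation.

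For x events versus 0 with 68 per arm, the two-sided Fisher P = 2 × C(68, x) / C(136, x):

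- x = 5: P = 0.058
- x = 6: P = 0.028

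So 6 versus 0 is the smallest significant split. The chance of reaching it is P(X ≥ 6) with X ~ Binomial(68, p):

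| True rate, both arms | Expected registered, SSC (68 × p) | Standard care | Chance of a false signal |
|---|---|---|---|
| 5% | 3.4 | 0 | 12% |
| 10% | 6.8 | 0 | 69% |
| 20% | 13.6 | 0 | over 99% |

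**4. Can respiratory events be recovered in both arms?**

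Clinical registration also lists oxygen requirement, hourly mode of breathing support, surfactant and mechanical ventilation, none restricted to one arm. The intubation outcome can therefore largely be derived for both arms. CPR is not among the listed items.

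**The case against.** The strongest reply is that the adverse-event rule is not the safety outcome. The outcome is defined under Outcomes measures, is arm-neutral, and can largely be derived from records kept in both arms. A bedside registration rule may legitimately differ from an outcome definition, and nothing says that registered events will be compared between arms. This stands, and it limits the bias to adverse-event registration and any comparison built from it.

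A second reply is that the key phrase can be read leniently, so that it sets aside simple interruptions of SSC and leaves room for standard-care events. This also stands as a possible reading. A reader might infer that standard-care infants can never be registered with a respiratory event; the text supports that only on the literal reading. The lenient reading still leaves an ambiguous rule without a standard-care equivalent, in the hands of unmasked staff.

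Third, the event rates are assumed. The plan excludes infants who need intubation, or CPAP with more than 40% oxygen at 10 minutes, so rates in this selected group may be low. At 5%, a false signal is unlikely (12%).

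Fourth, leaving thin-catheter surfactant or increased support out of the safety outcome is a defensible choice, since the plan describes surfactant by this route and CPAP as available treatment. That is accepted; the point is the mismatch between sections, not which criterion is right.

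**Conclusion.** The point holds as a should-fix. The respiratory adverse-event criterion is worded around the SSC pathway and has no standard-care counterpart. The sections also differ on respiratory criterion, CPR and time window, sharing only the 36 °C threshold where one is given. The temperature component applies equally to both arms.

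The size is uncertain. The 12% to over 99% range for a false signal requires the literal reading, equal true rates of 5% to 20%, complete registration in the SSC arm, and a between-arm test of registered events. Any standard-care registration under the lenient reading would reduce it.

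Two stronger inferences are not supported. One is that the stated safety outcome is itself biased: it is arm-neutral and largely derivable from data in both arms. The other is that the same infants would yield opposite safety conclusions depending on the section followed: the text shows that counts can differ, not that conclusions reverse.

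**What to change.** Reconcile the Abstract, Secondary aims, Secondary outcomes (Safety) and Clinical registration to one arm-neutral safety definition with one stated time window. Register it identically in both arms and list the components separately. The investigators should choose the clinical criterion for respiratory failure and the window.

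Derive respiratory events in both arms from the breathing-support, oxygen, surfactant and ventilation records already kept. Report SSC interrupted before 120 minutes, which is already recorded with its cause, separately as a feasibility measure for the SSC arm and not as a between-arm safety event.

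The cost is minor rewording and recoding of infants already enrolled: 27 by June 2016 according to Trial status. Two further hospitals join from January 2017, so the definition is best settled before they apply it. The case report form is not shown, so its wording should be checked against the article. Recoding may be incomplete, because hourly records can miss brief escalations and Clinical registration lists no CPR item.

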
#### Sociodemographic information

Information about education, employment (part- or full-time) and marital status is collected from the mothers’ medical records.

#### Consent and enrolment

Pregnant women admitted to the maternity ward at St. Olav’s University Hospital for anticipated preterm delivery between 28^0^–31^6^ weeks of gestation are eligible. Oral and written information about the study is provided by a pediatrician and/or a neonatal nurse, and written consent is obtained before delivery,

#### Randomization and allocation concealment

The randomization is done after the initial stabilization of the infant (Fig. 1). Infants are stratified by weeks of gestation (28^0^–29^6^ and 30^0^–31^6^). The randomization is conducted using sealed envelopes organized by the Unit for Applied Clinical Research at the NTNU.

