#### Sample size and statistical analyses

Primary analysis: sample size calculations are performed for a two-sample *t* test for comparing the Bayley Scale of Infant and Toddler Development, Third Edition, cognitive scale between the intervention (SSC) and control (SC) groups at 2 years of corrected age. To obtain a power of 80% for detecting a difference of 7.5 in mean score, using SD = 15 and significance level α = 0.05, 64 preterm infants are needed in each group. To allow for withdrawals, the sample size is set to 68 in each group.

Secondary analysis: differences between the SSC and SC groups for continuous variables will be analyzed using two-sample *t* tests, or Mann-Whitney *U* tests for data with non-normal distributions. Categorical variables will be analyzed by the Pearson chi-square test or Fisher’s exact test. *P* values <0.05 are considered statistically significant. Due consideration of multiple testing will be made when interpreting the results. All data will be presented and analyzed in accordance with the updated CONSORT guidelines for randomized trials [39].

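### Randomisation is stratified by gestational age, but every analysis named is an unadjusted two-sample test: a modest loss of efficiency, not an error

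*Protocol article*

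**What the plan says.** Under Randomization and allocation concealment: "Infants are stratified by weeks of gestation", with two bands, 28 weeks 0 days to 29 weeks 6 days and 30 weeks 0 days to 31 weeks 6 days.

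Under Sample size and statistical analyses, the paragraph labelled as the primary analysis states that "sample size calculations are performed for a two-sample *t* test for comparing the Bayley Scale of Infant and Toddler Development" on the cognitive scale at 2 years. The inputs follow: "To obtain a power of 80% for detecting a difference of 7.5 in mean score, using SD = 15 and significance level α = 0.05", from which "64 preterm infants are needed in each group". The paragraph says nothing else about how the primary outcome will be analysed.

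For the secondary outcomes, "differences between the SSC and SC groups for continuous variables will be analyzed using two-sample" t tests, or Mann-Whitney tests where normality fails. "Categorical variables will be analyzed by the Pearson chi-square test" or by Fisher's exact test. No stratum term, covariate or regression model appears anywhere in the article.

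Possible covariates are already being gathered. The case report form described under Clinical registration records gestational age, sex and birth weight, among others. Under Sociodemographic information: "Information about education, employment (part- or full-time) and marital status is collected" from the mothers' records.

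**The concern.** Stratifying the randomisation balances the two arms on gestational-age band. If the band predicts the Bayley score, that balance makes the difference between arms less variable than under simple randomisation. A pooled t test does not see this. It leaves the between-band variance in its error term, so the standard error is somewhat too large for the design used. Other baseline variables that predict the score, if they do, stay in the error term as well.

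At stake is the width of the confidence interval for the primary comparison, and the power. Recruitment is slow: Trial status reports 27 infants included from February 2014 to June 2016, against a target of 2 × 68 = 136. Precision that needs no further infants is worth having. Naming covariates before the 2-year results are known also prevents a choice made after seeing them.

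**Working it through.** **Inputs.** Difference 7.5 points, SD 15, α 0.05, power 80%, 64 per group (Sample size and statistical analyses). Sidedness is not stated; the two-sided calculation reproduces the number. The share of variance explained by baseline variables, R², is not in the article and is assumed.

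**1. The plan's own figure.** The standard error of the difference is 15 × √(2/64) = 2.652, and the noncentrality is 7.5 / 2.652 = 2.828. The noncentral t distribution with 126 degrees of freedom gives 80.1% power at 64 per group and 79.5% at 63. So 64 is correct for the unadjusted test. The target of 68 per group implies 4/68 = 5.9% withdrawals.

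**2. Adjusted comparison.** The residual SD becomes 15 × √(1 − R²), so the noncentrality becomes 2.828 / √(1 − R²), with one degree of freedom fewer. The equivalent unadjusted size is 64 / (1 − R²).

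| Assumed R² | Residual SD | Power at 64 per group | Equivalent unadjusted n per group | n per group for 80% power |
|---|---|---|---|---|
| 0 (unadjusted) | 15.00 | 80.1% | 64 | 64 |
| 5% | 14.62 | 82.1% | 67 | 61 |
| 10% | 14.23 | 84.1% | 71 | 58 |
| 15% | 13.83 | 86.1% | 75 | 55 |
| 20% | 13.42 | 88.1% | 80 | 52 |

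The standard error falls in proportion to √(1 − R²): by 2.5% at R² = 5% (√0.95 = 0.975) and by 10.6% at R² = 20% (√0.80 = 0.894). These figures treat infants as independent, as the plan's own calculation does.

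**3. The stratum alone.** If a share p of infants is in one stratum and the stratum means differ by d points, the stratum explains R² = p(1 − p)d² / 225. With p = 0.5:
- d = 3 gives 0.25 × 9 / 225 = 1.0%;
- d = 5 gives 0.25 × 25 / 225 = 2.8%.

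In 20,000 simulated trials per setting, with balanced allocation within strata, adding the stratum moved power from 80.5% to 80.8% (d = 3) and from 80.1% to 81.0% (d = 5). With d = 5, adding a further covariate that explains 10% or 20% of the variance brought power to 84.9% or 88.8%. Most of the gain therefore comes from the other covariates.

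**4. Type I error of the unadjusted test.** With balance on the stratum, the nominal 5% becomes about 2 × [1 − Φ(1.96 / √(1 − R²))]. This is 4.8% at a stratum R² of 2% and 4.4% at 5%. With equal strata, those values need d = √(0.02 × 225 / 0.25) = 4.2 points and d = √(0.05 × 225 / 0.25) = 6.7 points. The simulations gave 4.6% to 5.0% for the unadjusted test and 4.9% to 5.1% for the models with a stratum term.

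**The case against.** The strongest reply is that nothing in the article is invalid. An unadjusted comparison after stratified randomisation controls type I error, and the trial has the 80% power it was sized for under its own assumptions. This stands. A reader might infer that power already paid for is being thrown away, or that 64 per group is too few. Step 1 of the working supports neither.

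A second reply is that the article fixes no primary test. It names the t test as the basis for sizing, and a trial can be sized on a t test and analysed with a model; an analysis plan that is not shown may do so. This stands in part. The t test is, however, the only method offered in the primary-analysis paragraph, and the secondary tests are named outright as unadjusted. The point therefore concerns a stated choice and not only missing detail.

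A third reply is that nothing shows the collected variables to be strong predictors. This stands. The article lists them without saying how well they predict the 2-year score, and eligibility spans only four weeks of gestation. The timing of the education record is not stated either.

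A reader might also infer that adjustment would repair a loss of power from twins, who share an arm. At an assumed design effect of 1.18 and R² of 15%, the effective size is 64 / 1.18 / 0.85 = 63.8 per group, which looks like an exact offset. Both figures are assumptions: the article gives neither the twin rate nor the within-pair correlation. Gestational age and maternal education are also shared within a pair, so adjusting for them would change the residual correlation. No such offset can be claimed.

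Finally, a linear model does not suit rare events such as acute intubation or resuscitation. This stands, and the fix excludes them.

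**Conclusion.** The point holds as a modest and inexpensive gain in efficiency. The article stratifies the randomisation and then names only tests that ignore the stratum and the other baseline data. The sample size is right for the test named, and the error rate is controlled, if anything a little below 5%.

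The gain at 64 per group is about 2 to 8 percentage points of power if the covariates together explain 5% to 20% of the variance. It is about 1 point at most from the stratum alone, under an assumed 3 to 5 point difference between strata. Every R² here is an assumption, and correlation within twin pairs could take back part of the gain.

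**What to change.** Prespecify the primary analysis as a linear model of the Bayley-III cognitive score at 2 years corrected age on arm. Adjust for gestational-age stratum (or gestational age in weeks), sex and maternal education. Account for twin pairs, for example with a random pair effect or standard errors clustered on the mother. Keep the unadjusted comparison as a sensitivity analysis. Fix the covariate list before 2-year outcomes are examined, and define maternal education as its status at the birth.

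Adjust continuous secondary outcomes for the stratum in the same way. Keep exact or stratified methods for rare categorical outcomes.

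The cost is analysis wording. The covariates are already in the case report form or the mothers' records, and the sample size of 68 per group need not change on this account.
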